#### Pain Location and Chronicity

The number and location of painful anatomical sites will be assessed using the BPI-SF. Participants will complete Question 2 of the BPI-SF, which features a numerically coded body diagram showing 45 painful sites in the coronal (mediolateral) plane. Participants will self-report the duration of their chronic pain in months or years.

#### Pain Interference

In addition to the BPI, pain interference will be assessed using the Patient-Reported Measurement Information System (PROMIS) Pain Interference Short-Form 8a. The PROMIS Pain Interference Short-Form 8a assesses the impact of pain on social and recreational activities (65). Items are rated using a Likert scale and summed to compute a total raw score. Raw scores are then converted to a standardized T-score, with a mean of 50 for the general population. Higher T-scores (>50) indicate greater pain interference. The PROMIS Pain Interference Short–Form 8a has been validated in chronic pain populations (66, 67) and is available in Spanish (68).

#### Pain Behavior

Behaviors indicating that a person has experienced pain in the last 7 days will be assessed using the PROMIS SF v1.0 - Pain Behavior Short-Form 7a (69). Items are rated on a 6-point Likert scale, with responses ranging from “Had no pain” to “Always”. Items are summed to yield a total raw score, which is then converted to a standardized T-score. Higher T-scores (>50) indicate more pain behaviors. The PROMIS Pain Behavior Short-Form 7a has been validated in women with fibromyalgia(70).

#### Central Sensitization

The Central Sensitization Inventory (CSI) is a 25-item survey that queries symptoms indicative of central sensitization (71). The items ask how frequently respondents experience symptoms on a Likert scale with anchors from 0 (never) to 4 (always). The CSI total score ranges from 0 to 100, with higher scores indicating greater central sensitization. A score of 40 or higher yielded good sensitivity and specificity for detecting central sensitization(72). The CSI has been validated in multilingual populations with chronic pain(73).

### Biobehavioral Experimental Pain Assays

#### Pressure Pain Threshold

Mechanical pressure pain threshold (PPT) will be measured using a manual digital pressure algometer (Somedic AB, Farsta, Sweden) to assess both localized and widespread static pain sensitivity by activating Group III and Group IV muscle nociceptors (deep-tissue muscle afferents) (74, 75). Mechanical pressure will be applied using a 1cm^2^ algometer probe at a ramp rate of 50 kPa/sec. To ensure safety, the applied pressure will not exceed 700 kPa/sec. The three anatomical PPT testing sites are the muscle belly of the upper trapezius at the midpoint between the C7 vertebral spinous process and the acromion, the paraspinal muscles 1–2 cm lateral to the intervertebral space between the L2/L3 spinous processes (lower back)(76), and the medial knee joint line, the intercondylar space between the medial femoral epicondyle and the medial tibial condyle (21). These regions have previously been validated in adults with widespread pain (75). Pressure measurements will stop and be recorded once the participants press and release an external button connected to the device. Scripted participant instructions will be: “You will feel pressure at first. When you start to feel pain around 1 out of ten on the pain scale, press and release the red button.” These scripted instructions will also be given in conversational Spanish. There will be three repetitions at each anatomical testing site, and the mean PPT value in kilopascals (kPa) for each site will be used for all analyses. Lower PPT values indicate greater static pain sensitivity in deep-tissue muscle afferents. Details are outlined in **Supplementary Figure 1**.

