#### Cold Pressor Test (CPT)

We will also measure responses to noxious cold stimuli using a modified cold-pressor test (CPT)(77). Participants will be asked to submerge their non-dominant hand up to the wrist crease in a mixture of ice and water in a 10-liter (2.5-gallon) plastic pail. The water temperature will range from 8 °C to 12 °C, with a test duration of 2 minutes or until the participant reaches maximum tolerable pain to ensure participant safety. Participants will rate their pain intensity on a scale from 0 to 10 during and 30 seconds after hand immersion. During the CPT, we will also measure conditioned pain modulation (CPM), as outlined below. Cold pain intensity ratings and immersion time will be recorded and used in the analyses.

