#### Conditioned Pain Modulation (CPM)

We will perform conditioned pain modulation (CPM) to assess the function of descending inhibitory pathways responsible for endogenous analgesia (80). The total duration of CPM testing will be 2 minutes. We will use the parallel CPM paradigm, which has been shown to elicit a more robust inhibitory response in women with fibromyalgia (81). The test stimulus will be mechanical pressure applied at the upper trapezius using a pressure algometer contralateral to the hand submerged in cold water. The conditioning stimulus will be cold-water immersion of the non-dominant hand up to the wrist in an 8 °- 12 °C water bath. PPT will be measured immediately before (PPT1) and 60 seconds after (PPT2) cold water immersion. Pain intensity will be assessed at 20, 60, and 120 seconds after cold water immersion. The average of 3 PPT measurements at the upper trapezius will be included in the analyses. The percent change in PPT2-to-PPT1 values (PPT2/PPT1) × 100 and the absolute effect (PPT2 – PPT1) will be calculated. Lower values indicate impaired function of descending inhibitory pathways. This protocol has been used in women with fibromyalgia and higher BMI (82, 83). Details are outlined in **Supplementary Figure 3**.

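### The safety limit on pressure in the pressure pain threshold test is printed as a rate (700 kPa/sec); it should be a pressure, very probably 700 kPa

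*Protocol article*

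**What the plan says.** The Pressure Pain Threshold section of the protocol article describes testing with a manual digital algometer at three sites, three repetitions each. Four statements bear on this point:

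- Loading: "Mechanical pressure will be applied using a 1cm^2^ algometer probe at a ramp rate of 50 kPa/sec".
- Safety limit, in the next sentence: "To ensure safety, the applied pressure will not exceed 700 kPa/sec".
- End of a trial: "Pressure measurements will stop and be recorded once the participants press and release an external button connected to the device". The scripted instruction to the participant is "When you start to feel pain around 1 out of ten on the pain scale, press and release the red button".
- Unit of the result: "the mean PPT value in kilopascals (kPa) for each site will be used for all analyses".

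The section refers to Supplementary Figure 1 for details. That figure is not among the documents at hand.

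**The concern.** The limited quantity is a pressure, but the limit carries the unit of a rate of change of pressure. A rate limit and a pressure limit do different jobs. The first controls how fast the load rises; the second controls how high it goes. Only the second protects a participant who responds late or does not press the button. As printed, the only numeric ceiling on pressure in this test does not limit pressure.

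What is at stake is the wording of an operative safety threshold. The test is applied repeatedly: 3 sites x 3 repetitions = 9 ramps at Visit 1, and the battery is repeated at Visit 3. The same measure at the upper trapezius is used again in the Conditioned Pain Modulation section. The ceiling is also the largest threshold that a trial can record, so a reader needs its unit to know where values are cut off. The planned analyses do not depend on it otherwise.

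**Working it through.** This is a check of units with hand arithmetic. The limit is a set value, not a computed one, so there is no figure of the plan to reproduce.

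**Inputs, all from the Pressure Pain Threshold section**

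| Quantity | Printed value | Dimension |
|---|---|---|
| Ramp rate | 50 kPa/sec | pressure per time |
| Safety limit on applied pressure | 700 kPa/sec | pressure per time |
| Recorded threshold | kPa | pressure |
| Probe area | 1 cm² = 0.0001 m² | area |

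The second row is the odd one: it is described as a pressure but has the dimension of the first row, not the third.

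**Reading 1: the limit is a rate, as printed**

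- Ratio to the prescribed ramp: 700 / 50 = 14. An operator who keeps to the ramp is far below the limit throughout.
- Pressure after *t* seconds at the prescribed ramp is 50 x *t* kPa. At *t* = 20 s without a button press it is 50 x 20 = 1000 kPa, with the printed limit still met. The same holds for any longer time, so this reading gives no cap on pressure.

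**Reading 2: the limit is a pressure, 700 kPa**

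- Time to reach it at the prescribed ramp: 700 / 50 = 14 s.
- Force on the probe: 700,000 Pa x 0.0001 m² = 70 N.
- The limit now has the unit of the recorded threshold and stops the ramp at a definite point.

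Only the second reading agrees with the words of the sentence, with the separate ramp rate and with the unit of the outcome. A likely explanation is that the time unit was carried over from the sentence before.

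**Comparison with the next assay.** The Cold Pressor Test section states its stop as "with a test duration of 2 minutes or until the participant reaches maximum tolerable pain to ensure participant safety". Both parts of that rule bound the exposure itself. This is not evidence on the pressure unit, but it shows the form that a stopping limit should take.

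**The case against.** The strongest reply is that this is an obvious slip that the section corrects by itself. The sentence names a pressure, the ramp rate is stated separately and the result is in kPa, so a trained operator is unlikely to take the limit as a loading rate. In most trials the button press, made at the pain threshold, would be expected to end the ramp before any ceiling is reached. No endpoint definition, sample size or error rate is touched. This stands, and it is why the point is minor.

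Two further cautions also stand. The value 700 kPa appears nowhere in the text shown; it is an inference, and Supplementary Figure 1 may state the unit correctly. And because the algometer is manual, actual loading can depart from 50 kPa/sec, so it would go too far to say that a rate limit of 700 kPa/sec could never be reached. Even if it were, it would still not cap the pressure.

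The reply does not remove the error. The button press is the measurement endpoint and depends on the participant; the section does not present it as a safety stop. The fixed limit is the backstop for when the participant does not respond, and it is the number with the wrong unit. Nor is this detail that an article may leave to a fuller document: the article states the limit, and states it wrongly.

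**Conclusion.** The concern holds: the safety limit on applied pressure is wrong as written, because it is given in kPa/sec. Confidence in the unit error is high. That the intended value is 700 kPa is very probable but rests on inference from this one section. Taken literally, the limit is 14 times the prescribed ramp and leaves pressure uncapped; taken as 700 kPa, it acts at 14 s at the stated ramp.

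Severity is minor. The conclusion concerns the article's sentence only. It does not say that the study lacks a working limit in practice, and it has no bearing on sample size, power or type I error.

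**What to change.** In the Pressure Pain Threshold section, state the limit as a pressure in kPa, very probably 700 kPa, once the investigator has checked the value against the approved testing procedure and Supplementary Figure 1. The ramp rate of 50 kPa/sec stays as it is. The Conditioned Pain Modulation section needs no clause of its own, since it uses the same measure at a site already defined here.

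The cost is one corrected unit in one sentence, with no change to data collection or analysis. Recruitment and data collection are ongoing, so the correction is still useful to those carrying out the test as well as to anyone replicating it.

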#### Cold Pressor Test (CPT)

We will also measure responses to noxious cold stimuli using a modified cold-pressor test (CPT)(77). Participants will be asked to submerge their non-dominant hand up to the wrist crease in a mixture of ice and water in a 10-liter (2.5-gallon) plastic pail. The water temperature will range from 8 °C to 12 °C, with a test duration of 2 minutes or until the participant reaches maximum tolerable pain to ensure participant safety. Participants will rate their pain intensity on a scale from 0 to 10 during and 30 seconds after hand immersion. During the CPT, we will also measure conditioned pain modulation (CPM), as outlined below. Cold pain intensity ratings and immersion time will be recorded and used in the analyses.

#### Mechanical Temporal Summation (TS)

Mechanical temporal summation (TS) will be conducted with a predetermined stimulus intensity of 256 mN using a weighted pinprick stimulator (MRC Systems GmbH, Germany) to assess dynamic pain sensitivity. TS measurements will be taken at the intervertebral space between the L2/L3 spinous processes (lower back), which is the primary anatomical site of pain, as our previous work showed a higher prevalence of low back pain among racialized patients undergoing bariatric surgery (22). TS will also be measured at two remote anatomical sites: at the thenar eminence and the middle phalanx on the dorsum of the non-dominant hand (78). Pilot testing showed that 256 mN was best tolerated and elicited a summation response (data not shown). The anatomical location of the TS measurement was determined from prior literature on racialized Hispanic/Latino/a/X/e participants (79). Participants will be familiarized with the test using a single-probe application to the dominant forearm. The test will begin with a single pinprick stimulus, during which participants will verbally rate their pain intensity. There will be a single 10-train stimulus application, with the probe applied perpendicularly to the anatomical site at 1 Hz (1 cycle per second). Participants will be asked to verbally rate their pain immediately and 30 seconds after the 10^th^ stimulus. The absolute effect of TS will be calculated as the difference in pain ratings between the 1^st^ stimulus and the 10^th^ application at each anatomical site. A larger absolute effect of TS indicates greater dynamic pain sensitivity. Details are outlined in **Supplementary Figure 2**.

#### Conditioned Pain Modulation (CPM)

We will perform conditioned pain modulation (CPM) to assess the function of descending inhibitory pathways responsible for endogenous analgesia (80). The total duration of CPM testing will be 2 minutes. We will use the parallel CPM paradigm, which has been shown to elicit a more robust inhibitory response in women with fibromyalgia (81). The test stimulus will be mechanical pressure applied at the upper trapezius using a pressure algometer contralateral to the hand submerged in cold water. The conditioning stimulus will be cold-water immersion of the non-dominant hand up to the wrist in an 8 °- 12 °C water bath. PPT will be measured immediately before (PPT1) and 60 seconds after (PPT2) cold water immersion. Pain intensity will be assessed at 20, 60, and 120 seconds after cold water immersion. The average of 3 PPT measurements at the upper trapezius will be included in the analyses. The percent change in PPT2-to-PPT1 values (PPT2/PPT1) × 100 and the absolute effect (PPT2 – PPT1) will be calculated. Lower values indicate impaired function of descending inhibitory pathways. This protocol has been used in women with fibromyalgia and higher BMI (82, 83). Details are outlined in **Supplementary Figure 3**.

### Physical Function

Physical function and performance will be objectively measured at baseline (Visit 1) and at 6 months after bariatric surgery (Visit 3) using a modified Five-Time Sit-to-Stand Test (FTSTS) and the Six-Minute Walk Test (6MWT). Blood pressure, oxygen saturation, heart rate (beats per minute), and ratings of pain and fatigue intensity will be measured before and immediately after test completion. Participants will be asked to rate their MEP intensity as previously described and their level of perceived exertion at the 5-minute mark of the test. Perceived exertion will be assessed using the Borg Rate of Perceived Exertion (RPE)(84). During the FTSTS, participants will begin the test by sitting with their arms folded in their laps and their backs against a chair (45.7 cm (18 in) height × 48.3 cm (19 in) depth × 48.3 cm (19 in) width). Research personnel will instruct the participant to stand with the knees fully extended, then sit in a chair for 5 repetitions (85). The test will begin with the 1^st^ repetition and end after the 5^th^. The time required to complete the test, in seconds, will be included in all data analyses. The 5TSTS has been used in adults with fibromyalgia (15) and people who have had bariatric surgery (86). The 6MWT will be performed in accordance with a modified standardized protocol (87) to ensure participant safety and facilitate MEP assessment. Participants will complete the 6MWT in a corridor along a pre-measured 50-foot (15.2 m) walkway. All participants will receive standardized instructions in either English or Spanish before the test. Walking distance will be recorded in meters and included in all data analyses.

Participants will complete self-reported assessments of physical function. The PROMIS Short-Form v2.0 Physical Function 8b is a self-assessment of respondents’ abilities to perform a variety of physical activities using a 5-point Likert scale where responses range from “Without any difficulty” to “Unable to do”(88). Items are summed to yield a total raw score, which is then converted to a standardized T-score. Lower T-scores (<50) indicate worse physical function. The PROMIS Pain Interference Short-Form has been validated in adults with fibromyalgia(70, 89) and is available in Spanish.

The Lower Extremity Functional Scale (LEFS) assesses difficulty performing functional activities involving the lower extremities. Twenty items are rated on a 5-point Likert scale with anchors from 0 (“Extreme Difficulty/Unable to perform activity”) to 4 (“no difficulty”). The summative score for all items is the total score, ranging from 0 to 80. Lower scores indicate poorer lower-extremity function. Construct validity was moderate to good (r = 0.64 to 0.80) for the English version of the LEFS when compared with SF-36 physical function and physical component summary scores, and test–retest reliability (R = 0.86) and internal consistency (Cronbach alpha = 0.96) were excellent for the English version(90). The Spanish-translated version of the LEFS had high test-retest reliability (ICC=0.998, 95% CI: 0.996–0.999), high internal consistency (Cronbach’s *α* α = 0.989), and moderate to high concurrent validity with the SF-36 subscales (r=0.504–0.903)(91).

### Fatigue

Fatigue intensity will be assessed at the beginning of data collection (fatigue at rest) and before and after objective measures of physical function (movement-evoked fatigue). Fatigue intensity will be assessed using an 11-point rating scale ranging from 0 (no fatigue) to 10 (very fatigued). The PROMIS Short Form v1.0 – Fatigue 13a (FACIT-Fatigue) is a self-reported assessment of the frequency, timing, and severity of fatigue as well as the impact of fatigue on physical, cognitive, and social activities over the past 7 days (88). This survey is derived from the original Functional Assessment of Chronic Illness Therapy (FACIT), which was developed to assess health-related quality of life across health conditions (92). Items are rated on a 5-point Likert scale, with responses ranging from “Not at all” to “Very much”. Items are summed to yield a total raw score, which is then converted to a standardized T-score. Higher T-scores (<50) indicate greater fatigue. These measures have been validated in populations with localized and widespread pain (15, 89), but a minimal clinically important change has not yet been established.

### Psychological, Social, and Emotional Functioning

#### Pain Catastrophizing

Pain catastrophizing is a psychological phenomenon characterized by a tendency to amplify the perceived threat of a painful event, experience feelings of helplessness in the midst of pain, and ruminate about the pain before, during, or after a pain episode(93). The Pain Catastrophizing Scale (PCS) is a 13-item self-report instrument that evaluates levels of pain catastrophizing. Items on the PCS assess the extent to which participants experience magnification, rumination, or feelings of helplessness when in pain. Scores range from 0 to 52, with scores above 30 indicating clinically significant degrees of pain catastrophizing. The PCS is valid and reliable across multiple pain populations(94), and has been used in studies of patients who have undergone bariatric surgery(95), as well as in Spanish-speaking patients with fibromyalgia (Cronbach’s alpha = 0.79, ICC = 0.84(96)).

#### Perceived Stress

The Perceived Stress Scale-10 (PSS-10) assesses the level to which different situations are perceived as stressful over the past 30 days(97). Items query how frequently respondents endorse situations as stressful events on a 5-point Likert scale with anchors from 0 (never) to 4 (very often), with summative scores ranging from 0 to 40. Higher scores indicate greater levels of perceived stress. The PSS-10 demonstrates moderate internal consistency (Cronbach’s alpha > 0.70) across English and Spanish translations(97, 98).

#### Depression

Self-reported emotional distress as a result of a depressed mood will be assessed using the PROMIS Short Form v1.0 - Depression 8a questionnaire(99). Items are rated on a 5-point Likert scale, with responses ranging from “Never” to “Always”. Items are summed to yield a total raw score, which is then converted to a standardized T-score. Higher T-scores (<50) indicate higher levels of depression. The PROMIS Short Form v1.0 - Depression 8a questionnaire has been validated in patients who have undergone bariatric surgery (Cronbach’s alpha = 0.94; inter-item correlation (r = 0.69–0.88); item-scale correlations (r = 0.77–0.81))(100) and in racially and ethnically diverse adults(101).

#### Emotional Support

We will assess perceived levels of emotional support (e.g., being cared for, having a person to confide in) with the PROMIS SF v2.0 - Emotional Support 6a questionnaire(88). Items are rated on a 5-point Likert scale, with responses ranging from “Never” to “Always”. Items are summed to yield a total raw score, which is then converted to a standardized T-score. Lower T-scores (<50) indicate lower levels of emotional support. The criterion and construct validity of the PROMIS SF v2.0 - Emotional Support 6a questionnaire for English and Spanish-speaking populations is good(102), although the psychometric properties of the instrument for patients undergoing bariatric surgery have not yet been established.

#### Sleep Quality

We will assess sleep patterns and quality using the Pittsburgh Sleep Quality Index (PSQI). The PSQI survey is a self-reported assessment of sleep quality, latency, duration, disturbances, sleep efficiency, sleep medication use, and daytime functioning over the last month(103). The PSQI has 19 fixed-choice and open-ended items with 7 components. Component scores are derived from ratings on a 4-point Likert scale with anchors from 0 (no difficulty) to 3 (severe difficulty). The summative score for all components is the total score, ranging from 0 to 21. Higher scores greater than 5 indicate poor sleep quality. The PSQI has been validated in patients with fibromyalgia(104), in Spanish-translated versions(105), and for patients who have undergone bariatric surgery(106).

